## Abstract

**Background:**

Non-alcoholic fatty liver disease (NAFLD) is rapidly increasing alongside overweight and obesity, not only in adults but also in children and adolescents. It is unknown what impact the development of NAFLD in childhood may have in later life. The importance of early detection and treatment lies in its potential for progression to cirrhosis, liver cancer and liver-related death, as well as its associated extrahepatic comorbidities. Vibration-Controlled Transient Elastography (VCTE) with Controlled Attenuation Parameter (CAP) is an effective, non-invasive and safe diagnostic method to estimate the degree of fibrosis and steatosis in the liver, but little is known about its applicability in the paediatric population.

**Aims:**

1) To assess the prevalence of significant liver fibrosis (Liver Stiffness Measurement (LSM) ≥6.5 kPa) using VCTE, and that of non-alcoholic fatty liver disease (≥225 dB/m) using CAP in children and adolescents. 2) To determine the optimal cut-off points of the CAP to achieve maximum concordance with the Magnetic Resonance Imaging (MRI) findings in the diagnosis of mild, moderate and severe NAFLD in children and adolescents.

**Methods:**

Cross-sectional population-based study which will include 2,866 subjects aged between 9 and 16 years. Participants will undergo: anamnesis, physical examination, blood extraction, VCTE, MRI and questionnaires on socio-demographic data, personal and family medical history and lifestyle assessment.

**Applicability and relevance:**

The study aims to establish the foundations for the use of VCTE in children and adolescents in order to achieve early diagnosis of NAFLD. Moreover, it will serve to understand in further detail the disease and to identify the risk groups of children and adolescents who may be at risk of developing it. Ultimately, this will help determine to which subgroups of the population we need to target resources for prevention and early detection of this entity, as well as possible intervention for its treatment.

**Trial registration:**

The LiverKids study is registered on Clinicaltrials.gov (NCT05526274).

## Introduction

The increase of childhood obesity and its associated metabolic factors has led to an alarming rise in the incidence of non-alcoholic fatty liver disease (NAFLD) in this population. NAFLD is the accumulation of free fatty acids and triglycerides (TG) in the hepatocytes of individuals without toxic alcohol consumption and in the absence of other liver diseases. This pathology encompasses a wide spectrum of lesions ranging from simple steatosis to fibrosis, cirrhosis and even hepatocellular carcinoma [1].

NAFLD is the most common cause of liver disease and hypertransaminasaemia in the paediatric population, with a prevalence ranging from 7–9% and reaching 38–41% in obese children [2, 3]. Obesity is the main risk factor for NAFLD. The pathophysiological mechanisms are not yet fully understood, although the pathogenesis of NAFLD is considered to be multifactorial [4, 5]. The importance of early detection and appropriate management lies in its risk of progression to fibrosis and/or hepatocellular carcinoma along with its associated extrahepatic complications such as cardiovascular disease (CVD), diabetes mellitus (DM), insulin resistance (IR) and other endocrine and metabolic disorders like hypothyroidism or dyslipidaemia [6]. The presence of fibrosis is the major prognostic factor in NAFLD. Among children and adolescents with NAFLD, 25% have NASH and 14% have advanced fibrosis, the latter being more prevalent in paediatric patients with severe obesity than in adults with the same condition [7].

Diagnosis of NAFLD should be considered in paediatric population with excess weight, especially in those >10 years of age, with arterial hypertension (AHT), DM, IR or metabolic syndrome (MetS). In clinical practice, screening begins with anamnesis, physical examination, blood test and abdominal ultrasound, which help to establish a differential diagnosis with other entities. However, liver biopsy remains the gold standard for assessing disease progression, although its use is limited by its invasiveness and potential complications [8]. Some authors consider screening with transaminases, but these may still be normal in patients with NAFLD [5]. In terms of imaging, abdominal ultrasound, which is an affordable and safe technique, is only able to detect fatty infiltration above 30% [9]. Magnetic resonance imaging (MRI) is more accurate in diagnosing NAFLD, showing high sensitivity and specificity [10]. Nevertheless, its high cost and limited availability make it an invalid method for population screening.

Therefore, non-invasive serological and elastographic diagnostic methods are being developed. The most widely used is Vibration-Controlled Transient Elastography (VCTE), which non-invasively determines the presence of fibrosis by measuring liver stiffness (LSM) with the FibroScanⓇ (FS) device [11]. Multiple studies have demonstrated its usefulness in adults [11, 12], so it may also be appropriate for children and adolescents [5, 11]. Normal LSM values may vary according to age, ranging from 3.4–5.1 kPa [13, 14, 16]. Above this threshold, values correlate with different stages of fibrosis on the METAVIR scale: 5–7 kPa is indicative of F1; 7–9 kPa, F1-F2; and >9 kPa, F3-F4 [15, 16]. FibroScan features the Controlled Attenuation Parameter (CAP), which allows quantification of hepatic fat >11%. CAP values correlate with the degree of steatosis and a cut-off point of ≥225 dB/m is used for its detection [17, 18]. Furthermore, serological markers are used for diagnostic approaches to NAFLD and fibrosis. In adults, the Fatty Liver Index (FLI) [19] (NAFLD) as well as the NAFLD Fibrosis Score and FIB-4 (fibrosis) are commonly used [20] but these do not provide accurate results in the paediatric population [8, 21]. Thus, specific markers have been developed for these patients, such as the Pediatric NAFLD Fibrosis Index (PNFI) [22] and the Pediatric NAFLD Fibrosis Score (PNFS) [23], with an AUROC of 0.85 and 0.74 respectively [22, 23].

Ultimately, the only effective approach to prevent the progression of NAFLD and its associated comorbidities consists of lifestyle changes. Some studies have shown histological improvement after weight loss [24]. At present, no specific diet or physical exercise has been shown to improve the progression of NAFLD beyond the benefit of weight loss. Moreover, obesity and NAFLD tend to start developing at an early age and, in most cases, this development continues into adulthood with the hepatic, metabolic and cardiovascular consequences that this entails. Considering that any treatment is less effective in the late stages (F3-F4) of the disease compared to the early stages (F1-F2), screening for NAFLD as well as investigating the lifestyles and risk factors that may be related to it, especially from an early age, is key to its prevention and early management; this could have a very important health, social and economic impact [25].

## Study rationale and hypotheses

In recent years, large epidemiological studies are being conducted to screen for liver fibrosis in the adult population using non-invasive methods. These studies are showing alarming results regarding the increase of people with NAFLD mainly associated with overweight and obesity [12, 26]. It is known that children and adolescents with NAFLD are at greater risk of developing NASH and fibrosis in adulthood. Yet, there are no strategies for early detection of this entity among this population. In fact, the only studies performed using the CAP for the detection of NAFLD in children and adolescents, to date, have an extremely limited sample size, are conducted either in population at risk or with underlying liver disease, or their results are compared with non-accurate methods such as abdominal ultrasound [17, 27–30]. Hence, the main hypotheses stated in this study are: 1) Screening NAFLD using a non-invasive method such as VTCE in children and adolescents may be useful in detecting asymptomatic subjects with significant liver steatosis and fibrosis; and 2) The degree of NAFLD can be estimated by the CAP in a form analogous to that of MRI in children and adolescents.

Early detection of NAFLD in children and adolescents is key for its appropriate management and the prevention of its progression and that of its associated hepatic and extrahepatic complications. This would allow: a) to validate VCTE as a simple and safe screening method to advance in the early diagnosis of NAFLD in a highly vulnerable population such as paediatrics; and b) to determine to which subgroups of the infant-juvenile population we need to direct resources for the prevention and early detection NAFLD or any of its complications as well as the possible intervention for their treatment. Ultimately, all of this would allow the implementation of strategies aimed at halting NAFLD progression, thus preventing the development of severe related clinical outcomes in later life, which would result in adding additional years of healthy life.

### Study aims

The study main aims are: 1) To assess the prevalence of significant liver fibrosis (LSM ≥6.5 kPa) using VCTE, and that of NAFLD (≥225 dB/m) using the CAP in children and adolescents; and 2) To determine the optimal cut-off points of the CAP to achieve maximum concordance with the MRI findings in the diagnosis of mild, moderate and severe liver steatosis in children and adolescents.

### Study design

The present study has been registered on Clinicaltrials.Gov (NCT05526274) on 1^st^ September 2022. Inclusion of the first participant in the study took place in November 2022.

This is a cross-sectional and population-based study that will include 2,866 subjects in Catalonia (Spain). Eligible participants are being invited to join the study through informative talks held in their own educational centres. In these informative talks, for potential participants, their parents and their teachers, the date of the first visit is being scheduled and the socio-demographic data and medical history questionnaire are being distributed for participants to bring back completed on the day of Visit 1.

Visit 1 (V1): is carried out on all subjects, in the nurses’ offices of the educational centres. V1 includes: anamnesis, physical examination, VCTE to assess LSM and CAP, and collection of the completed socio-demographic and medical history questionnaire. After V1, all subjects are scheduled for Visit 2 and Visit 3. In addition, subjects with altered results (CAP ≥225 dB/m and/or LSM ≥ 6.5kPa) and 10% of subjects with normal results are referred to Visit 4. Lastly, subjects with suspected significant fibrosis (LSM ≥6.5 kPa) are referred to the Digestive Service of the Hospital Universitari Germans Trias i Pujol (HUGTP) for further evaluation (Visit 5).Visit 2 (V2): is conducted at the educational centres and consists on lifestyle assessment (Diet Quality estimation with the KIDMED index [31]), physical activity (PA) assessment with the Physical Activity Unified-7 item Screener (PAU-7S) [32], and sedentary behaviour [33], sleep duration [34], and sugar consumption assessment) through online self-reported questionnaires with the assistance of trained personnel.Visit 3 (V3): is performed in the Primary Care Centres corresponding to each subject. In V3, all subjects undergo blood sampling. The samples are analysed in the HUGTP laboratory.Visit 4 (V4): is performed in the Diagnostic Imaging Centres located within the area of the educational centres. MRIs are performed on all subjects with CAP ≥225 dB/m and/or LSM ≥6.5 kPa and 10% of participants with CAP <225 dB and/or LSM <6.5 kPa.Visit 5 (V5): is performed in the Digestive Service of the HUGTP. Subjects with suspected significant fibrosis (LSM ≥6.5 kPa) undergo the corresponding diagnostic tests and follow-up according the Clinical Practice Guideline for the Diagnosis and Treatment of NAFLD in Children [25].

Finally, all subjects (whether they obtain CAP ≥225 dB/m and/or LSM ≥6.5 kPa or CAP <225 dB/m and/or LSM <6.5 kPa), and especially those with NAFLD risk factors such as obesity, DM, MetS or risky alcohol consumption are counselled on lifestyle modifications by the health care professionals involved in the study [35]. They are also referred to their corresponding healthcare providers for management of these risk factors according to each centre’s own protocol (Fig 1).

**Fig 1 pone.0286586.g001:**
[figure not shown]
Study procedure flow chart. VCTE: Vibration-Controlled Transient Elastography; LSM: Liver Stiffness Measurement; CAP: Controlled Attenuation Parameter.

### Main outcome measures

Percentage of subjects with LSM ≥6.5 kPa by VCTE in the general population aged ≥9 to ≤16 years.Percentage of subjects with CAP ≥225 dB/m by VCTE in the general population aged ≥9 to ≤16 years.Comparison of liver steatosis diagnosis accuracy between CAP by VCTE and MRI in the general population aged ≥9 to ≤16 years.Determination of optimal cut-off points of the CAP for the diagnosis of mild, moderate and severe liver steatosis in children and adolescents.

### Specific outcome measures

Comparison of liver steatosis diagnosis accuracy between CAP by VCTE and Fatty Liver Index (FLI) in the general population aged ≥9 to ≤16 years.Comparison of liver fibrosis diagnosis accuracy between LSM by VCTE and two fibrosis scores (Pediatric NAFLD Fibrosis Index and Pediatric NAFLD Fibrosis Score) in the general population aged ≥9 to ≤16 years.Detection and structuring of the variables that constitute a specific biomarker for the paediatric-juvenile population that is capable of accurately determining the presence of hepatic steatosis.Correlation of liver steatosis diagnosis using CAP by VCTE, FLI and MRI, with the presence of lifestyles and socio-economic factors associated with NAFLD in the general population aged ≥9 to ≤16 years.Percentage of subjects with BMI ≥30 in the general population aged ≥9 to ≤16 years.Percentage of subjects with MetS according to the International Diabetes Federation (IDF) consensus criteria for children and adolescents [36] in the general population aged ≥9 to ≤16 years.

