### Statistical analyses

Prevalences of NAFLD and fibrosis will be calculated using CAP ≥225dB/m and LSM ≥6.5kPa, respectively. They will be calculated by sex and age (9–12 and 13–16 years) and 95% confidence intervals will be provided.To determine the optimal CAP cut-off point that best fits the 4 MRI categories, the relationship between CAP and MRI will be explored graphically, CAP means for each MRI category will be compared by ANOVA, 2-to-2 ROC curves will be used, and a multi-class ROC curve will be used to obtain the overall area under the curve for the finally chosen points. In addition, dichotomous CAP classifications (normal/altered) will be compared with MRI levels using contingency tables and chi-square tests.To identify the variables related to NAFLD, multivariate models will be used using NAFLD as the dependent variable and possible risk and confounding factors as independent variables.Concordance between the diagnosis of NAFLD or fibrosis obtained by different methods (CAP vs FLI, LSM vs PNFI, LSM vs PNFS) will be assessed by kappa indices (when using the dichotomised version of these variables) and by the intraclass correlation coefficient (when using the continuous version of the variables). The best cut-off point in PNFI and PNFS will be chosen to detect fibrosis using LSM ≥6.5 kPa as the standard test in the diagnosis of fibrosis using ROC curves.The construction of the biomarker to detect the presence of steatosis in children and adolescents will be carried out using the coefficients of multivariate logistic regression models, where steatosis (CAP >225 dB/m) will be the dependent variable and the rest of the variables will be potential explanatory variables that may form part of the marker.

To take into account that participants come from selected schools, hierarchical models will be used when necessary. All tests will be bilateral, with a significance of 5%. We do not plan to use missing data imputation methods as we expect very few missings beyond those already considered. Stata17 statistical package will be used.

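### The CAP–FLI outcome is worded as diagnostic accuracy, but the pair is analysed only by agreement (kappa and ICC), which cannot show which test is more accurate

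*Protocol article*

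**What the plan says.** - **Outcome.** The protocol article, Specific outcome measures, lists "Comparison of liver steatosis diagnosis accuracy between CAP by VCTE and Fatty Liver Index (FLI") in the general population aged 9 to 16.
- **Analysis of that pair.** Statistical analyses plans "Concordance between the diagnosis of NAFLD or fibrosis obtained by different methods (CAP vs FLI, LSM vs PNFI, LSM vs PNFS"). For dichotomised values this "will be assessed by kappa indices (when using the dichotomised version of these variables"); for continuous values it is assessed "by the intraclass correlation coefficient (when using the continuous version of the variables").
- **MRI.** The Introduction states: "Magnetic resonance imaging (MRI) is more accurate in diagnosing NAFLD, showing high sensitivity and specificity". Statistical analyses uses MRI against CAP: "To determine the optimal CAP cut-off point that best fits the 4 MRI categories", with pairwise and multi-class ROC curves, ANOVA and contingency tables. It states no analysis of FLI against MRI. The one other outcome that names CAP, FLI and MRI together concerns their correlation with lifestyle and socio-economic factors.
- **FLI in children.** Of the adult scores, FLI included, the Introduction says "but these do not provide accurate results in the paediatric population".
- **Numbers.** Sample size calculation expects 2,866 children, 8% with NAFLD, blood in 50% (1,433 tests) and 424 MRIs. MRI is offered to all LSM/CAP positives and to a random 10% of negatives.

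**The concern.** Accuracy is defined against a reference. Kappa and the ICC compare two index tests with each other, and swapping the tests leaves kappa unchanged. If CAP and FLI disagree, neither statistic can separate FLI missing steatosis from CAP over-calling it at 225 dB/m. CAP cannot simply stand in as the reference, because its cut-off points are themselves under study in the second main aim.

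The outcome as worded would therefore go unanswered. A reader who also has the Introduction's view of FLI could take a low kappa as confirming it, although CAP error would give the same result.

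This is not a detail left to a fuller document. The article names the pair and fixes the statistics for it.

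**Working it through.** **1. The plan's own counts.** Blood: 0.5 × 2,866 = 1,433, as stated. MRI: 0.7 × 0.08 × 2,866 = 160.5 positives, plus 0.10 × 0.92 × 2,866 = 263.7 negatives, total 424.2 (stated 424). The 70% uptake is thus applied to the positives only.

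**2. Kappa cannot rank the tests.** Assumed inputs (not in the protocol, except the 8%): prevalence 0.08; errors independent given true status. Scenario A: CAP 0.90/0.95 (sensitivity/specificity), FLI 0.50/0.98. Scenario B: the reverse.

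Scenario A:
- CAP positive: 0.08 × 0.90 + 0.92 × 0.05 = 0.118
- FLI positive: 0.08 × 0.50 + 0.92 × 0.02 = 0.0584
- both positive: 0.08 × 0.90 × 0.50 + 0.92 × 0.05 × 0.02 = 0.0369
- both negative: 1 − 0.118 − 0.0584 + 0.0369 = 0.8605
- observed agreement: 0.0369 + 0.8605 = 0.8974
- chance agreement: 0.118 × 0.0584 + 0.882 × 0.9416 = 0.8374
- kappa = (0.8974 − 0.8374) / (1 − 0.8374) = 0.369

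Scenario B only exchanges the two discordant cells, so kappa is again 0.369. The symmetry is a property of kappa and does not depend on the chosen values.

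**3. One table, two readings.** Assumed: CAP positive 8.0%, FLI positive 3.32%, both 2.4%, so the cells are 0.024, 0.056, 0.0092 and 0.9108. Observed agreement is 0.9348 and chance agreement 0.8921, giving kappa 0.396.
- If CAP is right, FLI has sensitivity 0.024/0.08 = 30% and specificity 0.9108/0.92 = 99%.
- If FLI is right, CAP has sensitivity 0.024/0.0332 = 72%, specificity 0.9108/0.9668 = 94% and PPV 0.024/0.08 = 30%.

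**4. How many children could support an MRI-referenced comparison.** FLI needs triglycerides and GGT, hence blood. If blood and MRI uptake are independent (assumption): 424 × 0.5 = 212, of whom 263.7 × 0.5 ≈ 132 are VCTE-negative. Without that assumption the overlap can lie anywhere from 0 to 424.

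**5. Why weighting is needed.** Take MRI as the truth, treat CAP status as VCTE status, and use MRI fractions of 0.7 (positives) and 0.1 (negatives). Unweighted, CAP in scenario A shows
- sensitivity 0.072 × 0.7 / (0.072 × 0.7 + 0.008 × 0.1) = 0.984 instead of 0.90
- specificity 0.874 × 0.1 / (0.874 × 0.1 + 0.046 × 0.7) = 0.731 instead of 0.95

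In scenario B, CAP shows 0.875/0.875 instead of 0.50/0.98. Inverse weights undo this. In scenario A, (0.0504/0.7) / (0.0504/0.7 + 0.0008/0.1) = 0.072/0.080 = 0.90.

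**6. What weighting costs.** A VCTE-negative child carries weight 1/0.1 = 10, against 1/0.7 = 1.43 for a positive child. Expected FLI-positive/CAP-negative children with both MRI and blood (cell × 2,866 × 0.1 × 0.5):
- table in step 3: 0.0092 gives 1.3
- scenario A: 0.0584 − 0.0369 = 0.0215 gives 3.1
- scenario B: 0.118 − 0.0369 = 0.0811 gives 11.6

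**The case against.** **The word accuracy may just be loose.** The article uses the same phrasing for CAP against MRI and for LSM against the fibrosis scores, where two methods are set side by side without a third. On that reading the CAP–FLI item means agreement, and the analysis paragraph does speak of concordance. This has force, and it is why rewording is half of the fix. But in the CAP–MRI comparison MRI is the more accurate method, and the score cut-offs are chosen with LSM named as the standard test. For CAP and FLI no standard is named.

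**Kappa is not the only planned statistic.** A reader might infer that it is; the plan also has an ICC. The ICC does not fill the gap. It too lacks a reference, and CAP (dB/m) and FLI (an index with cut-off 60) are on different scales.

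**The illustrative values are not trial data.** Correct. The documents give no FLI-positive rate and no joint CAP–FLI rate. The tables show a property of kappa and do not measure harm in this study. Nor do the documents say that a low kappa will be read as FLI failing; that is only a risk.

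**The MRI-referenced analysis may not rank the tests either.** This stands. MRI is sampled on CAP/LSM, and one discordant cell may hold as few as one child, while agreement can use up to 1,433 children.

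**Conclusion.** The point holds: the outcome is worded as accuracy, the analysis fixed for it measures agreement, and agreement cannot show whether CAP or FLI is the more accurate. That conclusion needs no assumed numbers. The figure of 212 children rests on independent blood and MRI uptake, and the roughly 132 VCTE-negative children rest on that plus the plan's 8% prevalence.

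A reader might infer that the study leaves MRI unused, or that its main diagnostic question is compromised. The documents support neither. CAP is compared with MRI by ROC curves and contingency tables, and the prevalence estimates and sample size do not depend on the CAP–FLI analysis. The defect is confined to one specific outcome and should be corrected at low cost.

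**What to change.** 1. In children with CAP, FLI and MRI, estimate sensitivity and specificity (at CAP ≥225 dB/m and FLI ≥60) and AUC of each test against MRI steatosis. Make the comparison paired, weight by the inverse of the MRI sampling probability (all CAP/LSM positives, 10% of negatives, allowing for the uptake achieved), and give confidence intervals.
2. Label this comparison exploratory, and report the number of children in each discordant cell.
3. Keep the CAP–FLI kappa in all children with blood as a description of agreement. Word that outcome as agreement between CAP and FLI, and state that no conclusion about which test is more accurate will be drawn from kappa.

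**Cost.** One added analysis of data already planned, and a change of wording. The comparison uses fewer children than the kappa (about 212 against up to 1,433). Weighted sensitivities will be imprecise, because they depend on the few steatotic children among about 132 heavily weighted VCTE-negative children, and the FLI-positive/CAP-negative cell may be nearly empty.

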### Recruitment and enrollment of participants

Subjects aged between 9 and 16 years who are enrolled in the compulsory education system in the territory of Mataró (Catalonia). Eligible patients have been identified following the EU General Data Protection Regulation (GDPR-2018) and then randomised and stratified by schools and institutes. These educational centres have a social class value (high/middle/low) assigned according to the MEDEA variable [37] and are differentiated by type (charter/private or public). A number of educational centres have been randomly selected from each social class-type combination, taking into account the number of students enrolled in each educational centre in order to reach the necessary sample that is representative of the students attending school in Mataró.

General practitioners and primary care nurses invite subjects to participate in the study from schools. Informative talks are held at the educational centres in which the legal guardians of the subjects are informed about the study and are requested to give their written informed consent for their children’s participation. Once subjects and/or their legal guardians accept to participate in the study, they are scheduled a visit at their own educational center where they are informed about the details of the study and enrolled if they meet the selection criteria outlined below.

*Inclusion criteria*: subjects between 9 and 16 years of age whose legal guardians have provided written informed consent for their children’s participation in the study. Subjects over 12 years of age are also required to give their own written informed consent.*Exclusion criteria*: subjects with previously diagnosed liver disease, receiving hepatotoxic drug treatment, with eating disorders diagnosed prior to study entry and/or children/adolescents who do not attend class on the day of the measurements.

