Anthropometric data: weight (kg), height (cm), Body Mass Index (BMI) [38–40], waist circumference (WC) [40] and thoracic circumference.Tanner’s pubertal stage: it classifies and divides pubertal changes into five successive stages, ranging from infant (grade I) to adult (grade V).Determination of blood pressure.**Analytical determination** is performed on all subjects, after 12 hours of fasting, at the Primary Care Centre. It includes:Blood count, glucose, glycosylated haemoglobin, basal insulin levels, total cholesterol, high-density lipoprotein (HDL), low-density lipoprotein (LDL), triglycerides (TG), aspartate transaminase (AST), alanine transaminase (ALT), gamma-glutamyl-transpeptidase (GGT), alkaline phosphatase (ALP), total bilirubin, sideremia, transferrin, transferrin saturation index, total protein, albumin, urea, creatinine, sodium, potassium, thyroid stimulating hormone (TSH) and tiroxine (T4).Determination of insulin resistance using the HOMA method: blood glucose (mmol/L) x insulin (mU/L)/22,5.

**Metabolic Syndrome (MetS)** is determined according to the IDF consensus criteria for children and adolescents [36]. These include a WC at the ≥90th percentile and the presence of 2 or more of the following variables: 1) TG ≥150 mg/dl, HDL <40 mg/dl. 2) Blood pressure ≥130/85 mmHg. 3) Blood glucose ≥100 mg/dl or previously diagnosed DM.

**Liver fibrosis** is estimated by two methods: LSM and liver fibrosis scores.

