## Conclusions

The LiverKids study will allow us not only to assess the current prevalence of both NAFLD and liver fibrosis in the infant-juvenile population but to understand in further detail the comorbidities associated with childhood obesity and to identify the risk groups of children and adolescents who, without being obese, may be at risk of developing NAFLD or any of its complications. Thus, once these factors have been established, we will be able to determine to which subgroups of the population we need to direct resources for the prevention and early detection of these entities as well as the possible intervention for their appropriate management. In addition, the validation of VCTE as a non-invasive, simple and safe method will allow to progress in the early diagnosis of chronic liver diseases in an easy and safe way in a highly vulnerable population such as paediatrics.

Framing NAFLD screening as a challenge for preventive practices will give us the opportunity to avoid the development of the advanced stages of the disease and its severe outcomes such as liver cirrhosis, hepatocarcinoma and/or liver-related death, as well as its multiple associated extrahepatic comorbidities.

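### The BMI ≥30 outcome uses one fixed value for ages 9 to 16, so as a measure of obesity it is stricter in younger children and under-counts most among them

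*Protocol article*

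**What the plan says.** Under Specific outcome measures, the protocol article includes "Percentage of subjects with BMI ≥30 in the general population aged ≥9 to ≤16 years". One number applies to the whole age range and both sexes, with no percentile, z-score or growth reference.

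Under Data collection and measuring tools, BMI appears only as a measurement: "Anthropometric data: weight (kg), height (cm), Body Mass Index (BMI) [38–40], waist circumference (WC) [40] and thoracic circumference". Three references are cited, but the text gives no classification rule. The same section lists obesity among the comorbidities taken in the clinical history, without a criterion. For metabolic syndrome it uses paediatric consensus criteria, of which it says "These include a WC at the ≥90th percentile".

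Obesity matters to the study's argument. The Introduction states "Obesity is the main risk factor for NAFLD", and the Conclusions promise "to identify the risk groups of children and adolescents who, without being obese, may be at risk of developing NAFLD"; Expected results makes the same promise.

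**The concern.** BMI is not on a constant scale during growth. Its typical value rises between 9 and 16 years, so a fixed cut-off marks a different relative position at each age. A 9-year-old has to be much further from the middle of the age group than a 16-year-old before being counted.

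Two things follow for the outcome as written. As a measure of obesity it misses children who would be classed as obese against their own age and sex, and it misses most of them at the young end. The single percentage for ages 9 to 16 also adds together groups judged by criteria of unequal strictness, so it depends on the age mix of the sample as well as on adiposity.

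A further consequence is conditional. If the same cut-off were used as a covariate, for comparisons between ages, or to form the group of non-obese children, some younger children with obesity would be placed among the non-obese.

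**Working it through.** **1. The text, side by side.**
- BMI outcome (Specific outcome measures): fixed at 30, ages 9 to 16.
- BMI measurement (Data collection and measuring tools): references 38–40 cited, no rule in the text.
- Waist circumference (same section): a percentile.
- Obesity in the clinical history (same section): no criterion.
- Non-obese children at risk (Expected results, Conclusions): no criterion.

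Nothing in the article replaces the fixed 30 or defines obesity in another way.

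**2. Does the sample size depend on this outcome?** The inputs from Sample size calculation are 11,503 pupils in four roughly equal groups, fibrosis 2% ± 1% and NAFLD 8% ± 2% per stratum, design effect 20% and alpha 5%.
- Population per stratum: 11,503 / 4 = 2,875.75.
- Fibrosis: n0 = 1.96² × 0.02 × 0.98 / 0.01² = 752.9. With finite population correction, 752.9 / (1 + 752.9 / 2,875.75) = 596.7. Rounded up, 597 × 1.2 × 4 = 2,865.6, which gives the stated 2,866.
- NAFLD: n0 = 1.96² × 0.08 × 0.92 / 0.02² = 706.8, corrected 567.4. Then 567.4 × 1.2 × 4 = about 2,723, which is smaller.

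The stated N is reproduced from the fibrosis precision alone. No BMI figure enters it.

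**3. Direction and possible scale.** The article gives no BMI distribution, so these inputs are assumptions for illustration: lognormal BMI; median 16.5–17.5 at age 9, 18.5–19.5 at age 12 and 20.5–21.5 at age 16; CV 0.15–0.20. Formulas: s = √ln(1 + CV²); z = ln(30 / median) / s; share counted = 1 − Φ(z); BMI at +2 SD = median × exp(2s).

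Worked ends of the range:
- Age 9, median 16.5, CV 0.15: s = 0.149, z = 0.598 / 0.149 = 4.01.
- Age 9, median 17.5, CV 0.20: s = 0.198, z = 0.539 / 0.198 = 2.72.
- Age 16, median 20.5, CV 0.15: z = 0.381 / 0.149 = 2.55.
- Age 16, median 21.5, CV 0.20: z = 0.333 / 0.198 = 1.68.

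| Age | z of BMI 30 | Share with BMI ≥30 | BMI at +2 SD |
|---|---|---|---|
| 9 | 2.72 to 4.01 | 0.003% to 0.3% | 22.2 to 26.0 |
| 12 | 2.18 to 3.24 | 0.06% to 1.5% | 24.9 to 29.0 |
| 16 | 1.68 to 2.55 | 0.5% to 4.6% | 27.6 to 31.9 |

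For any one CV, BMI 30 is a stricter criterion at 9 than at 12, and at 12 than at 16. If +2 SD is taken as an arbitrary common mark, 30 lies above it at 9 and 12 in every scenario and on either side of it at 16. The under-count is therefore clear at the young end; at the oldest ages it depends on the distribution and on the reference chosen. The illustration makes no separate calculation by sex.

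**The case against.** The strongest reply is that the outcome line does not use the word obesity. It asks for one overall percentage, and as a plain description that percentage is correct whatever 30 means at each age. References 38–40 may contain paediatric BMI standards, and the full protocol may define obesity properly. The waist criterion does not establish a general rule of age adjustment either, since the same metabolic syndrome definition uses fixed values for triglycerides, HDL, blood pressure and glucose. This is also a descriptive specific outcome, and a z-score can be derived later from data already collected.

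Much of this stands, and it limits the point. The contrast with waist circumference is not an internal contradiction. What the cited references contain is unknown. Three stronger readings are tempting, and the article does not support them:
- **That the age and sex groups will be reported on a non-comparable basis.** The statement "They will be calculated by sex and age (9–12 and 13–16 years) and 95% confidence intervals will be provided" refers to the NAFLD and fibrosis prevalences. No breakdown of BMI ≥30 by age or sex is stated, and the effect of sex has not been sized.
- **That NAFLD among non-obese children will be inflated.** Nothing says that BMI ≥30 defines that group or enters the risk-factor models.
- **That the percentage will be near zero at 9–12 years.** No figure in the article shows this, and even the assumed distributions reach 1.5% at age 12.

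The explicit threshold remains. It is a stated definition and not a detail left out for brevity. In a study that treats obesity as central, it is hard to see what the outcome is for if not to describe obesity. If the cited references do hold paediatric standards, the outcome line needs to be reconciled with them.

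**Conclusion.** The point holds as a badly fixed outcome definition. As a measure of obesity in 9- to 16-year-olds, BMI ≥30 under-counts, most in the youngest, and its pooled percentage mixes criteria of unequal strictness. This rests on two premises: that BMI rises with age through childhood, and that the outcome is meant to represent obesity. The second is an inference, though the article offers no other obesity outcome or definition.

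The size cannot be computed from the article; the tabulated ranges show direction under assumed inputs and are not estimates for this population. Misclassification in other analyses is a risk only if the same cut-off is reused there. The prevalence aims, the comparison of CAP with MRI and the sample size are untouched. The change is worth making, but it does not threaten the study's main results.

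**What to change.** Reword the outcome as the percentage of participants with obesity, defined by an age- and sex-specific BMI percentile or z-score from one named growth reference. Check that reference against references 38–40, which the article already cites for BMI, and reconcile the outcome line with them. Use the same variable wherever obesity status enters an analysis, including the risk-factor models and the identification of non-obese children at risk. BMI ≥30 can stay as a descriptive line.

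The cost is one reworded definition and one derived variable. Weight, height, age and sex are already collected, so there are no new measurements or visits, and N stays at 2,866.
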